### Data collection and outcome measures

Table 
1 displays the outcome measures and corresponding timepoints. Demographic data (including age, sex, post code, contact details, nominated General Practitioner (GP)), psychiatric, and self-report measures are obtained from each participant at baseline and post intervention (3-months) to determine depressive and anxiety symptoms, functioning and quality of life (using the Assessment of Quality of Life 8 dimension [AQoL8D]
[25]) which will also allow the calculation of quality-adjusted life-years (QALYs). Clinical data such as blood pressure and anthropometric measures including height, weight and waist circumference are also taken. Habitual dietary patterns are collected as stated above. The IPAQ
[24] and self-report smoking questionnaire are completed. At 6-months, participants are contacted via telephone during which time RAs re-administer the MADRS, Hospital Anxiety and Depression Scale (HADS)
[26] and DST. At this time, participants initially assigned to the control condition are offered the resources developed and used by the APD for the diet intervention.

**Table 1 T1:** Schedule of measurements

**Variable**	**Instrument**	**Time point**
**Self-report**		
Diet quality	Diet screening tool [18]	Screening, 6-months^#^
Psychiatric conditions	SCID-I/NP*	Screening
Personality disorders	Standardised Assessment of Personality – Abbreviated Scale (SAPAS) [19]	Screening
Depression	MADRS* [17]	Screening, baseline, 3-, 6-months^#^
Anxiety	Hospital anxiety depression scale [26]	Baseline, 3-, 6-months
Depression severity	Clinical global impressions scale [27]	3-months
Mood	Profiles of Moods State (POMS) [28]	Baseline, 3-months
Quality of life, utility, wellbeing	Assessment of Quality of Life (AQoL-8D) [25]; WHO wellbeing scale [29]	Baseline, 3-months
Diet intake	Food Frequency Questionnaire (FFQ) [23]	Baseline, 3-months
Physical activity	International Physical Activity Questionnaire (IPAQ) [24]	Baseline, 3-months
Smoking	Self-report	Baseline, 3-months
Medications	Self-report	Baseline, 3-months
Medical conditions (including family history)	Self-report (Doctor diagnosed) depression, anxiety, myocardial infarction, angina, hypercholesterolemia, high blood pressure, diabetes	Baseline, 3-months
Health care resource utilisation	Self-reported hospitalisations, attendances at physicians, psychologists, allied health, complementary and alternative medicine providers	Baseline, 3-months
Self efficacy	General Self Efficacy Scale (GSE) [30]	Baseline, 3-months
Participant satisfaction	Diet preference score	3-months
Lost productivity	Self-reported time lost from paid and unpaid work	Baseline, 3 months
**Anthropometric & clinical**		
Waist, weight, height, blood pressure	Height to nearest 0.1 cm. Body weight to nearest 0.1 kg. BMI = weight divided by height squared kg/m^2^, Digital metre	Baseline, 3-months
**Biochemical**		
Erythrocyte fatty acids and cartenoids	Venous blood sample (fasting)	Baseline, 3-months
High-density lipoprotein, Lower-density lipoprotein, total cholesterol	As above	Baseline, 3-months
Triglycerides, blood glucose	As above	Baseline, 3-months

* clinician administered; ^#^6-month assessment via telephone. Baseline= pre-intervention, 3-months= post-intervention, 6-months= 3-months post-intervention.

Health care resource utilization is captured through self-report and includes information on the quantity and reasons for hospitalisations, numbers of visits to health care providers and complementary and alternative medicine practitioners as well as any out-of-pocket costs related to services for both mental and physical health. Previous studies have found associations between MDE and high total resource utilization and costs (both mental and physical disorders)
[31,32]. Randomisation should distribute underlying characteristics that may confound between-group comparisons and will be evaluated by analysis of baseline data. Lost productivity is similarly self-reported using questions to capture time away from paid and unpaid work due to health problems (absenteeism), in addition to time working while suffering from health problems (presenteeism).

Blood samples are prepared by the nominated laboratory as per the standardised protocol. Once prepared, samples are temporarily stored in −20 degree freezers and then transferred to −80 degree freezers at the Department of Dietetics and Human Nutrition, La Trobe University, Bundoora and Barwon Health, Geelong until assays are performed in batches. Erythrocyte fatty acids and plasma carotenoids represent important markers of dietary intake/change in both groups. Erythrocyte fatty acids will be analysed at the Metabolic Research Unit, Deakin University. Retinol, alpha- and gamma-tocopherol and carotenoids (lutein + zeaxanthin, beta-cryptoxanthin, lycopene and alpha- and beta-carotene) in plasma will be processed and analysed by High Pressure Liquid Chromatography at La Trobe University.

Dietary intake is assessed for each participant at baseline and post intervention to evaluate intake relative to the Australian Dietary Guidelines. Detailed information on foods and fluids consumed are collected using 7-day food diaries at the beginning and end of the intervention (1–7 days preceding the first session and 1–7 days preceding the final session) to monitor adherence to the intervention. These dietary assessments are also administered to the control group to capture any dietary changes made while being involved in the study.

RAs conducting data collection are blinded to participants’ group allocation. Prior to each assessment, participants are reminded not to reveal the group to which they have been assigned.

### Data management

The RA at respective sites are responsible for electronic scanning and storage of hard copies of case report forms (CRFs) for entry into the password protected central database by the respective RAs. Hard copies are kept in a secure filing cabinet at the respective sites. If requested, participants can access their individual results at the completion of the study period, by making a direct request to the CTC.

### Study integrity

Approval to conduct the study was received from Human Research Ethics Committees of St. Vincent’s Hospital Barwon Health and Deakin University. Written informed consent is obtained from all participants. This study has been developed in accordance with CONSORT guidelines. Safety protocols have been developed at each site to monitor the welfare of participants whose condition may deteriorate throughout the course of the study, with senior psychiatric consultants (DC, MB) overseeing this process.

### Sample size

We are aiming to recruitment 88 participants per group, assuming attrition of 15% over 6-months (leaving 70 individuals per group eligible for evaluation), with 8 predictors (including potential confounding variables). For a one- tailed analysis with α=0.05, the study will be powered at 80% to detect a true difference in rating scale score between the diet and befriending groups if the effect size is 0.15 or greater.

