**Methods/Design:**

One hundred and seventy six eligible participants suffering from current MDE are being randomised into a dietary intervention group or a social support group. Depression status is assessed using the Montgomery–Åsberg Depression Rating Scale (MADRS) and Structured Clinical Interview for Diagnostic and Statistical Manual of Mental Disorders (Non Patient Edition) (SCID-I/NP). The intervention consists of 7 individual nutrition consulting sessions (of approximately 60 minutes), delivered by an Accredited Practising Dietitian (APD). Sessions commence within one week of baseline assessment. The intervention focuses on advocating a healthy diet based on the Australian Dietary Guidelines and the Dietary Guidelines for Adults in Greece. The control condition comprises a befriending protocol using the same visit schedule and length as the diet intervention. The study is being conducted at two locations in Victoria, Australia (a metropolitan and regional centre). Data collection occurs at baseline (pre-intervention), 3-months (post-intervention) and 6– months. The primary endpoint is MADRS scores at 3 months. A cost consequences analysis will determine the economic value of the intervention.

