## Methods

### Study design

This is a 12-week, parallel group, single blind, randomised, controlled trial of a dietary intervention for the treatment of moderate to severe depression. We are currently enrolling 176 participants over two sites; Barwon Health in Geelong and St. Vincent’s Health in Melbourne (Victoria, Australia). Recruitment and intervention are anticipated to occur over a 1.5-2 year period. Participants are randomised to receive either the dietary intervention or a control condition (social support). Participants in both groups complete assessments prior to program commencement (baseline), at program completion (3-months) and at a 6-month follow-up (via telephone).

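### The three sample-size figures do not agree: 15% attrition from 88 per group leaves about 75, not 70, and the protocol does not show which figure is wrong

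*Protocol article*

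**What the plan says.** The Sample size section sets the recruitment target: "We are aiming to recruitment 88 participants per group". The same sentence derives the evaluable number from it, "assuming attrition of 15% over 6-months (leaving 70 individuals per group eligible for evaluation". It then adds the model size, "with 8 predictors (including potential confounding variables". The next sentence gives the power statement: "For a one- tailed analysis with α=0.05", power is put at 80% for an effect size of 0.15 or more, with no metric named for that effect size.

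The target of 88 is not a misprint confined to this section. The abstract gives a total of one hundred and seventy-six, and the Study design section says "We are currently enrolling 176 participants over two sites"; 2 × 88 = 176. No other section gives a second attrition rate, or a further loss between attrition and evaluability.

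**The concern.** The sentence presents 70 as what remains of 88 after 15% attrition, and simple multiplication does not give 70. At least one of the three numbers (88, 15% or 70) must therefore be something other than what was used in planning.

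The evaluable number is the input to the power claim. As written, a reader cannot tell whether power was worked out for 140 participants (2 × 70), for about 150 (2 × 75), or on some other basis. The recruitment target is in the same position: at the stated attrition rate, fewer than 88 per group would deliver 70.

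**Working it through.** **Inputs, all from the Sample size section**
- Recruited per group: 88 (176 in total, confirmed in the abstract and Study design)
- Attrition: 15% over 6 months
- Evaluable per group: 70 (140 in total)

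**1. Reproduce the stated 70 from 88 and 15%**

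Evaluable = recruited × (1 − attrition) = 88 × 0.85 = 74.8, about 75.

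The stated figure is 70, so the gap is 74.8 − 70 = 4.8 per group, or 4.8/70 = 6.9%. Rounding does not explain it.

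**2. Hold two figures and solve for the third**

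| Held fixed | Solved for | Result |
|---|---|---|
| 88 and 15% | evaluable | 88 × 0.85 = 74.8, about 75 per group (176 × 0.85 = 149.6 in total) |
| 88 and 70 | attrition | 1 − 70/88 = 20.5% |
| 70 and 15% | recruited | 70/0.85 = 82.4, so 83 per group (166 in total) |

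**3. Try other dropout conventions**
- Multiplying up instead of dividing: 70 × 1.15 = 80.5, so 81. Not 88.
- Dividing down: 88/1.15 = 76.5. Not 70.
- 15% lost in each of two periods: 88 × 0.85 × 0.85 = 63.6. Not 70.
- 20% attrition: 70/0.80 = 87.5, rounded up to 88. This fits.

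Of the conventions tried, only an allowance of about 20% connects 88 and 70.

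**4. Direction of the error**

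Correct any one figure and leave the other two as they stand:
- evaluable number corrected: about 75 per group;
- attrition corrected: 70 per group;
- recruitment corrected to 83: 83 × 0.85 = 70.6 per group.

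In none of these cases does the evaluable number fall below the stated 70.

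**5. Effect on power**

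The protocol does not name the metric of its effect size of 0.15, so two readings are shown as assumptions, solely to compare 70 with 75 per group.

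- *Read as a standardised mean difference*, one-sided α = 0.05, unadjusted: power = Φ(0.15 × √(n/2) − 1.645).
  - n = 70: Φ(0.887 − 1.645) = 22%.
  - n = 75: Φ(0.919 − 1.645) = 23%.
- *Read as Cohen's f² in a regression with 8 predictors, all tested jointly*: noncentral F with 8 and N − 9 degrees of freedom and noncentrality 0.15 × N.
  - N = 140: 91%.
  - N = 150: 93%.

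The difference between 70 and 75 is one to two percentage points under either reading.

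**The case against.** **Evaluability may be narrower than retention.** Participants might be retained yet not be evaluable, which could bring 75 down to 70. That would need a further loss of 4.8/74.8 = 6.4%. No such loss is stated anywhere, and the parenthesis reads as the direct result of the 15%. This does not close the gap.

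**The consequence is slight.** This stands. The slip is conservative, power barely moves, and enrolment need not change. In addition, the Data analyses section plans intention to treat, a likelihood-based repeated-measures model and multiple imputation, so the analysis is not confined to a fixed set of completers. These points limit the weight of the finding but do not make the figures agree.

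**Stronger readings that the document does not support**
- *That attrition is stated at the wrong time.* The abstract says "The primary endpoint is MADRS scores at 3 months", so a reader might infer that a 6-month attrition figure is an error. But the Data analyses section describes the primary efficacy analysis as covering the whole of the study, and a 6-month MADRS assessment is planned. Cumulative loss by 6 months is also at least as large as loss by 3 months, so the allowance is conservative.
- *That the trial would be judged against 15%.* Nothing in the protocol makes the attrition rate a conduct threshold, a trigger or a success criterion.
- *That the slip leaves the trial underpowered.* It does not. Whether 80% power follows from an effect size of 0.15 is a separate question, and this point takes no weight from it.

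**Conclusion.** The inconsistency is real and can be checked from one sentence: 88 per group, 15% attrition and 70 evaluable cannot all hold. The discrepancy is about 5 per group (about 10 in total). In terms of attrition it is 20.5% implied against 15% stated; in terms of recruitment it is 83 needed against 88 planned.

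A reader might conclude that 15% is simply a misprint for 20%. That is the neatest explanation, but it is an inference. The document equally allows that 70 was miscalculated, or that 88 was set higher than the stated assumptions require.

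The error is conservative and its effect on power is small, on the assumption that only one of the three figures is wrong. It still merits correction rather than being passed over as clerical, because it concerns a number on which the stated power rests.

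**What to change.** Keep enrolment at 88 per group and restate the sentence so that the figures agree, in one of two ways:

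- about 20% attrition assumed over 6 months, leaving 70 per group; or
- 15% attrition assumed over 6 months, leaving about 75 per group.

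Then state the power for whichever evaluable number is kept. The sponsor should choose from the original planning calculation, since the article alone cannot settle which figure was intended.

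The cost is one sentence and a check of the power figure. Recruitment, visits and analysis are unaffected.

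### The 80% power at effect size 0.15 does not follow from the printed inputs for the diet-versus-befriending contrast, and the effect-size index is not named

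*Protocol article*

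**What the plan says.** The Sample size section of the protocol article gives these inputs:

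- Recruitment: "We are aiming to recruitment 88 participants per group".
- Loss: "assuming attrition of 15% over 6-months", "leaving 70 individuals per group eligible for evaluation".
- Model: "with 8 predictors (including potential confounding variables").
- Test: "For a one- tailed analysis with α=0.05".
- Claim: the trial is "powered at 80% to detect a true difference in rating scale score between the diet and befriending groups if the effect size is 0.15" or more.

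The section does not say whether 0.15 is d, f, f-squared or another index. It gives no SD, no difference in MADRS points and no correlation between visits.

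The Data analyses section says only that effect sizes will follow Cohen's guidelines. It plans a repeated-measures mixed model averaged over the study period, and an analysis of covariance of change from baseline. The Abstract makes MADRS at 3 months the primary endpoint.

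**The concern.** This paragraph is the only justification the article gives for its sample size. It is worded as a one-tailed comparison of two group means, so the natural reading of 0.15 is a standardised mean difference. On that reading 70 per group falls far short of 80% power. The mention of eight predictors points instead to f-squared in a multiple regression, and the usual power calculation for that model concerns a different hypothesis.

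Two things are at stake. A reader cannot tell how large a benefit the trial was designed to detect. And the power quoted may belong to a test other than the treatment comparison.

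**Working it through.** **Inputs, all from the Sample size section.** n = 70 per group (N = 140), one-sided alpha 0.05, eight predictors, effect size 0.15, claimed power 80%.

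**1. Trying to reproduce the 80%.** For two means, the noncentrality is d × √(n/2), with √(70/2) = 5.916. The test uses 138 degrees of freedom and a one-sided critical value of 1.656. For the eight-predictor omnibus F test, the noncentrality is f² × N on 8 and 131 degrees of freedom.

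| Reading of 0.15 | Noncentrality | Power |
|---|---|---|
| Cohen's d = 0.15 | 0.15 × 5.916 = 0.887 | 22% |
| Cohen's f = 0.15, so d = 2f = 0.30 | 0.30 × 5.916 = 1.775 | 55% |
| f² = 0.15, omnibus test of eight predictors | 0.15 × 140 = 21.0 | 91% |
| f² = 0.15, treatment term alone, one-sided (d = 2√0.15 = 0.77) | √21.0 = 4.58 | 99.8% |

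None gives 80%. On the omnibus reading, 80% would need only 109 participants in total.

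**2. Does the evaluable number explain it?** 88 × 0.85 = 74.8, so 15% attrition leaves about 75 per group. A final 70 implies (88 − 70)/88 = 20.5% loss. Neither 75 nor the full 88 per group restores 80%: d = 0.15 gives 23% and 26%, and f = 0.15 gives 57% and 63%.

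**3. Does adjustment for baseline explain it?** Assume a common correlation ρ between visits; the article states none. Adjusting a single follow-up visit for baseline multiplies the variance by 1 − ρ². Adjusting the mean of two follow-up visits multiplies it by (1 + ρ)/2 − ρ². The effective d is d divided by the square root of that factor. With 70 per group, one-sided 0.05:

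| ρ (assumed) | d = 0.30, one visit | d = 0.30, mean of two visits | d = 0.15, one visit | d = 0.15, mean of two visits |
|---|---|---|---|---|
| 0.3 | 58–59% | 76–77% | 24% | 32% |
| 0.5 | 65–66% | 80–81% | 27% | 35% |
| 0.7 | 80% | 90–91% | 34% | 43% |

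Ranges show the small gap between the noncentral t and normal calculations. At ρ = 0.5 with two visits, the factor is 0.75 − 0.25 = 0.50 and the effective d is 0.30/√0.50 = 0.424. At ρ = 0.7 with one visit, the factor is 0.51 and the effective d is 0.420. Both come to about 80%. For d = 0.15, no entry exceeds about 43%.

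**4. What the sample does detect.** Solving the unadjusted two-mean calculation for 80% power:

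| Evaluable per group | One-sided 0.05 | Two-sided 0.05 |
|---|---|---|
| 70 | d = 0.42 | d = 0.48 |
| 75 | d = 0.41 | d = 0.46 |

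Detecting d = 0.15 with 80% power, one-sided and unadjusted, would need about 550 per group. The article gives no MADRS SD. If it were 8 to 10 points (an assumption), d = 0.42 would be 0.42 × 8 = 3.4 to 0.42 × 10 = 4.2 points.

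**The case against.** A reader might infer that no reading of 0.15 gives 80%. That goes too far. The Data analyses section plans baseline adjustment and a model over both follow-up visits, and with f = 0.15 either assumed-correlation route in step 3 gives about 80%. This part of the objection stands. It does not make the printed claim verifiable, because neither correlation is in the article. The two-visit route also averages 3 and 6 months, whereas the Abstract names MADRS at 3 months as the primary endpoint. For that single visit, ρ = 0.5 gives only about 66%.

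A reader might also infer that the trial has 22% power for its planning effect. That holds only if 0.15 is Cohen's d, which the article never says. If the authors meant f-squared, as the eight predictors suggest, 80% is below the computed 91% and the figure is conservative. The difficulty is then the hypothesis: the omnibus test asks whether eight variables jointly explain the score. It does not isolate diet from befriending, and an F test on eight degrees of freedom cannot be one-tailed.

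Finally, one might fear that a null result would be taken to exclude small effects. The plan commits to 95% confidence intervals, and those will show what a null result excludes, so this risk should not be overstated.

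**Conclusion.** The statement is wrong as written. Its 80% does not follow from its own inputs for the contrast it names, and the index is undefined. Depending on the index, the same inputs give anything from 22% to over 99%. The only routes found to about 80% use f = 0.15 with an unstated correlation.

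If 0.15 was meant as a standardised mean difference, the detectable effect is understated by a factor of nearly three (0.42/0.15 = 2.8), and correlations of 0.3 to 0.7 do not close the gap. The step 4 figures assume equal groups, a common SD and no covariate adjustment, so they would improve with a justified baseline correlation. The finding concerns the stated planning basis. It does not show that 176 participants is too few.

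**What to change.** Keep the enrolment target and rewrite the paragraph:

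1. Name the index behind 0.15 and any correlation the calculation used.
2. Replace the 0.15 and eight-predictor statement with the detectable treatment difference for MADRS at 3 months, at the planned one-tailed alpha of 0.05 and 80% power. Without covariate adjustment this is d = 0.42 with 70 per group or 0.41 with 75. The two-sided equivalents, 0.48 and 0.46, may be given for reference.
3. If a gain from baseline adjustment is claimed, state the correlation and its basis.
4. Give the corresponding difference in MADRS points under a stated SD.
5. Reconcile the attrition: either about 75 evaluable per group at 15%, or 70 per group with about 20% loss.

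The cost is one paragraph of wording, with no extra participants and no change to the analysis. The stated detectable effect becomes less favourable if 0.15 was meant as a standardised mean difference.

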### Data analyses

Data analysis will be conducted by a researcher blinded to the treatment conditions. A one-tailed analysis will be used to detect differences in MADRS scores between the intervention and control groups. Analyses will explore dose–response effects associated with intervention diet adherence. The primary efficacy analysis will assess average treatment group differences for the primary outcome measure (MADRS) over the entire study period and use a likelihood based mixed-effects model, repeated measures (MMRM) approach at each time point. Analysis of covariance (ANCOVA) will be used to compare differences between treatment means in changes from baseline to follow up. Intention to treat analysis will be employed. To assess confounding, covariates will include age, gender, Body Mass Index (BMI) physical activity levels, smoking and alcohol consumption. Non-parametric statistics will be used when assumptions for parametric methods are violated. Effect sizes will be calculated using Cohen’s guidelines. All tests of treatment effects will be conducted using an alpha level of 0.05 and reporting 95% confidence intervals. Multiple imputation will be employed for the management of missing data.

The economic evaluation will compare the dietary intervention to its comparator (the befriending group) in terms of both the costs and consequences as assessed by an incremental cost-effectiveness ratio (ICER). The primary study design is that of a cost consequence analysis (CCA)
[33].

Standard Australian unit costs (i.e. Medicare Benefits Schedule) will be applied to the resource use units collected. Costs will be presented in total and disaggregate forms such as those falling upon the health sector, patients, government and other sectors. The technique of ‘bootstrapping’ will be used to obtain confidence intervals for cost effectiveness ratios, since parametric techniques are inappropriate for use on skewed variables and ratios. The sensitivity of the results will also be tested against the variation in the utility weights and unit cost prices.

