### Study aims

We aim to investigate the efficacy of dietary improvement in the treatment of MDE. The primary outcome includes changes in MDE using the Montgomery-Åsberg Depression Rating Scale (MADRS). Secondary outcomes include; depressive and anxiety symptoms, functioning, quality of life, and changes in targeted dietary behaviours, cardiovascular and metabolic risk. A secondary aim is to evaluate the cost efficacy of the intervention from a societal perspective at 3 months.

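### The primary endpoint is MADRS at 3 months, but the primary analysis averages MADRS over 3 and 6 months, so the deciding contrast is not fixed

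*Protocol article*

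**What the plan says.** The Abstract (Methods/Design) fixes the endpoint and its time: "The primary endpoint is MADRS scores at 3 months". Study aims names the same scale as the primary outcome but gives no visit.

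Data analyses defines the deciding analysis differently: "The primary efficacy analysis will assess average treatment group differences for the primary outcome measure (MADRS) over the entire study period". The same sentence says that this analysis will "use a likelihood based mixed-effects model, repeated measures (MMRM) approach at each time point". The next sentence adds a further comparison and gives it no rank: "Analysis of covariance (ANCOVA) will be used to compare differences between treatment means in changes from baseline to follow up". That sentence names neither MADRS nor a visit.

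The visits come from two places. The Abstract says "Data collection occurs at baseline (pre-intervention), 3-months (post-intervention) and 6– months", and Table 1 lists MADRS at "Screening, baseline, 3-, 6-months". The table footnote places the 6-month assessment three months after the intervention and notes that it is done by telephone. Data analyses also states that treatment comparisons on MADRS are one-tailed and that every treatment test uses alpha 0.05.

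**The concern.** A difference at 3 months and an average difference over 3 and 6 months are the same quantity only if the effect is the same at both visits. The first asks whether people are less depressed when the dietary sessions end. The second mixes that question with whether the benefit lasts three months without sessions. The Abstract makes the first primary and Data analyses makes the second primary; no sentence reconciles them.

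Two things are at stake. First, the power of the deciding test depends on which contrast is used, and the difference can be large in either direction. Second, if the two results disagree, each can be defended from the protocol text as the pre-specified primary result. Blinding the analyst to treatment labels does not remove that choice.

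**Working it through.** **The texts side by side.** MADRS has two post-baseline visits, 3 and 6 months.

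- Endpoint (Abstract): difference at 3 months, δ₃.
- Primary analysis (Data analyses): average over the study, (δ₃ + δ₆)/2 with equal weights.
- These agree only if δ₆ = δ₃.

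The conflict is established at this point. The arithmetic below only shows its possible size.

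**The plan's own figure.** Sample size gives 88 per group, 70 evaluable, one-tailed 0.05, 80% power and an effect size of 0.15, without naming the metric or the visit. This does not reproduce. Read as a standardised difference, 0.15 needs 550 per group, and 70 per group give 22% power. Read as Cohen's f² with 8 predictors, at most 109 participants in total are needed. That is a separate matter, but it means that 0.15 cannot calibrate this check.

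**Inputs.**
- From the protocol: n = 70 per arm, one-sided α = 0.05, 80% power.
- Solved from those: d₃ = (1.645 + 0.842) × √(2/70) = 2.486 × 0.169 = 0.42.
- Assumed, because the document gives neither: correlation ρ between the 3- and 6-month scores of 0.5 to 0.7, and the fraction f of the effect kept at 6 months (1, 0.5 or 0). The SD is taken as equal at both visits.

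**Power of the averaged contrast.** Its effect is d₃(1 + f)/2 and its SD factor is √((1 + ρ)/2), so the noncentrality is

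[0.42 × (1 + f)/2] / √((1 + ρ)/2) × √(70/2).

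Example, ρ = 0.5 and f = 0.5: 0.42 × 0.75 = 0.315; 0.315/0.866 = 0.364; 0.364 × 5.916 = 2.15. Power from the noncentral t with 138 df is 0.690.

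| Effect kept at 6 months | ρ = 0.5 | ρ = 0.6 | ρ = 0.7 |
|---|---|---|---|
| All | 0.887 | 0.869 | 0.850 |
| Half | 0.690 | 0.666 | 0.643 |
| None | 0.414 | 0.396 | 0.381 |

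The 3-month contrast has 0.80 in every cell. A normal approximation gives values higher by less than 0.005.

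**Break-even.** The average has more power than the 3-month contrast when (1 + f)/2 > √((1 + ρ)/2). For ρ = 0.5 this means f > 2 × 0.866 − 1 = 0.73; for ρ = 0.7, f > 2 × 0.922 − 1 = 0.84.

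**False-positive chance if success may be read from either contrast.** With no effect, the 3-month and averaged test statistics correlate at √((1 + ρ)/2), that is 0.866 for ρ = 0.5 and 0.922 for ρ = 0.7. The chance that at least one exceeds 1.645 is 0.071 and 0.066 respectively. Over the wider range ρ = 0.3 to 0.9 it is 0.075 to 0.059. With a single fixed contrast it is 0.05.

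**The case against.** **The study period might end at 3 months.** Study design calls this a 12-week trial and describes the 6-month contact as a telephone follow-up. A repeated-measures model with baseline as a response would still have two time points. But only one post-baseline MADRS would be left, so there would be nothing to average as a treatment effect. The same section also lists the 6-month contact among the assessments, and Sample size counts attrition over 6 months. The wording could be clearer, but this reading does not fit it.

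**The analysis plan may settle it.** Ranking of supportive analyses is commonly left there, and its absence here is no fault. Two statements that conflict on the deciding test are a different matter: an analysis plan could follow only one of them.

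**A reader might infer several competing primary p-values, with the ANCOVA among them.** The text does not support that. The ANCOVA is unranked and not tied to MADRS; it could equally serve outcomes measured only at baseline and 3 months. A false-positive chance of 8–9% (at correlations of 0.7 and 0.5) arises only if success could be claimed on any of the 3-month, 6-month and averaged contrasts. The statements in conflict concern two of these, which gives about 7%, and even that supposes a choice made after seeing the results.

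**A reader might infer that averaging dilutes the effect the trial was sized for.** This is not shown either. Sample size names no visit, and nothing in the document predicts fading. The final diet session is meant to support lasting change, and controls are offered the diet resources only at the 6-month contact. If the effect persists, the average is the more powerful contrast.

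**Conclusion.** The concern stands as a conflict between the named primary endpoint (3 months) and the stated primary analysis (average over the study, with by-visit results in the same sentence). It can be seen from the text without calculation, and it affects the test that decides the efficacy claim.

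Its size depends on values the document does not give. With 70 per arm, d = 0.42 at 3 months and a correlation of 0.5 to 0.7, moving from the 3-month to the averaged contrast changes power from 80% to anywhere between 38% and 89%, depending on how much effect remains at 6 months. Leaving the choice open between the two raises the false-positive chance from 5% to about 7%. The power figures are illustrations and do not forecast a loss. The conclusion does not extend to the ANCOVA as a rival primary analysis.

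**What to change.** Replace the primary-analysis sentence in Data analyses with wording such as: *The single primary analysis is the between-group difference in MADRS at 3 months, estimated as the 3-month contrast from an MMRM that includes the 3- and 6-month visits. The 6-month contrast and the average over visits are secondary.* Add the 3-month visit to the primary outcome in Study aims so that all three places agree.

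The ANCOVA need not be deleted. If it is applied to MADRS, label it a sensitivity analysis at 3 months; otherwise name the outcomes it covers.

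Aligning the analysis with the endpoint is preferable to the reverse, because the protocol describes enrolment as under way and changing the Abstract would change the primary endpoint of a running trial. The cost is a wording change: the model, visits and data stay the same. It should be made before any outcome data are compared by group.
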